### Methods in analysis to handle protocol non-adherence and any statistical methods to handle missing data {20c}

The main outcome in the final analysis will be presented according to the intention to treat principle. No imputation will be performed. Complications will be handled with an as-treated analysis.

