### Criteria for discontinuing or modifying allocated interventions {11b}

All participants are free to withdraw from study participation at any time. If any complications such as stiffness, infection, or pain should occur, they will be treated according to local routines. All results will be presented according to the intention-to-treat principle.

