### Static Two-Point Discrimination test (S2PD)

The primary outcome of this study is the return of sensation 12 months after nerve injury, assessed using the S2PD, measured in millimeters. S2PD is the most widely used test to evaluate sensory function in the fingers [7]. The S2PD test evaluates tactile spatial acuity i.e. the ability to distinguish between two separate points of contact on the skin. The S2PD test, initially described by Weber in 1834, and later modified by Moberg [7] is performed using the Mackinnon-Dellon Disk-Criminator™ by applying two pins longitudinally over the radial and ulnar sides of the fingertip, with distances ranging from 0 to 25 mm. The minimum distance at which an individual can accurately distinguish between one or two points is recorded as the S2PD value. The test will be conducted in a standardized manner, ensuring that the pins are applied with just enough pressure to cause skin blanching [8], as excessive force may stimulate other receptors rather than mechanoreceptors responsible for pressure sensation [9, 10]. The injured finger is examined, as well as the corresponding finger on the uninjured hand for comparison. A correct response in seven out of ten random applications is required for a valid measurement.

Classification of sensory recovery according to the Mackinnon-Dellon scale [11], modified from the Highet classification, will be used. Sensation is classified as: Poor = >15 mm, Good = 7–15 mm, Excellent = 2–6 mm. The test and its validity have been questioned [12, 13].

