### Participant timeline {13}

#### Sample size {14}

This study was designed as a prospective superiority trial, aiming to determine whether one treatment strategy resulted in a superior sensory recovery outcome compared to the other. The primary endpoint was the proportion of participants achieving recovery of sensibility, defined as S2PD ≤ 10 mm, measured at the 1-year follow-up.

A power calculation was performed based on the assumption of a 20% clinically meaningful difference between groups. Using a two-sided significance level of *p* < 0.05 and a statistical power of 80%, the required sample size was calculated to be 150 patients. This calculation was based on an expected outcome proportion derived from a previously published study [38]. To account for an anticipated dropout rate of 10%, the total sample size was adjusted to 166 participants.

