## Statistical methods

### Statistical methods for primary and secondary outcomes {20a}

Primary outcome is a dichotomous outcome that will be presented as proportions of patients obtaining return of 2PD < 10 mm 1 year after injury, presented with 95% confidence interval, and proportions between groups will be compared with Chi^2^ analysis.

All numerical values will be tested for normality by Shapiro–Wilk’s test.

We assume normality/parametric data for age, AROM, and grip strength. Results are presented as numerical values on an interval scale. Central tendencies of data will be described as means with their corresponding standard deviation, and comparisons between groups will be performed with Student’s *t*-test or repeated measures ANOVA.

Categorical data will be presented as proportions and compared by Chi^2^ analysis, unless Fisher’s exact test is demanded due to expected small numbers. Ordinal data will be presented as medians and interquartile range (IQR), and Mann–Whitney *U*-tests or Wilcoxon’s test used for comparisons between groups.

We assume a skewed distribution for time to injury, sick leave, and PROMs, which will be presented as medians with IQRs and compared by Mann–Whitney *U*-tests or Wilcoxon’s test.

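### The primary analysis is called intention-to-treat but, with imputation ruled out, is an observed-case comparison with no missing-data sensitivity analysis; fingers with no measurable discrimination have no stated code

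*Protocol article*

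**What the plan says.** Section {20c} of the protocol article, on non-adherence and missing data, makes two statements in succession: "The main outcome in the final analysis will be presented according to the intention to treat principle", and then "No imputation will be performed". Section {11b} is broader still: "All results will be presented according to the intention-to-treat principle".

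Section {20a} makes the primary outcome dichotomous at 1 year and says that "proportions between groups will be compared with Chi" square analysis. Section {14} describes the endpoint as recovery "defined as S2PD ≤ 10 mm, measured at the 1-year follow-up", and adds: "To account for an anticipated dropout rate of 10%, the total sample size was adjusted to 166 participants".

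Section {20b} adds a mixed model for the primary outcome. It lists covariates such as age, smoking, level of injury and time to treatment, and then says that nothing further is planned by way of additional or subgroup analysis. Table 1 schedules S2PD at allocation, 3 weeks, 3, 6 and 12 months.

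The S2PD section describes a device covering 0 to 25 mm, records the smallest distance that is discriminated, and says: "A correct response in seven out of ten random applications is required for a valid measurement". Its worst recovery class is open-ended, above 15 mm. It does not say what is entered when a finger fails at every distance.

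**The concern.** Intention to treat has two parts: participants are analysed in the arm to which they were allocated, and all randomised participants are kept. The plan secures the first. The second cannot be met by a single-time-point chi-square test when missing outcomes may not be filled in, because a participant without a 12-month result has no cell in the table.

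The trial is unblinded, and its Discussion names loss to follow-up as a possible source of bias. If the reasons for missing the 12-month visit relate to both arm and recovery, the observed-case difference is biased, and nothing in the plan would show by how much. The earlier S2PD values, which carry information on the missing outcomes, are not stated to be used.

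The uncoded result is a second, separate gap. A finger with no discrimination up to 25 mm is among the worst outcomes. If the data handler reads the seven-of-ten sentence as making such a result invalid, the finger could leave the denominator although its status is known.

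**Working it through.** **1. The plan's own figure.** Inputs from section {14}: 150 analysable participants and 10% dropout. 150 / 0.9 = 166.7, which rounds up to 167; 150 × 1.1 = 165. The stated 166 is within one participant of either, so it reproduces closely enough.

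**2. How many are left out.** 166 − 150 = 16 participants without a 12-month result, or 8 per arm if 166 splits 83/83 and losses are equal (assumed).

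**3. What those 16 could do.** Assumed observed results: 60/75 recovered after surgery and 45/75 after cast. The documents give no base proportion. The test is the pooled two-proportion z, equivalent to chi-square without continuity correction: z = (p1 − p2) / √[p(1 − p)(1/n1 + 1/n2)].

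- Observed cases: 0.80 − 0.60 = 20.0 points. Pooled p = 105/150 = 0.70, standard error = √(0.21 × 2/75) = 0.0748, z = 2.67, p = 0.008.
- All missing counted as not recovered: 60/83 − 45/83 = 15/83 = 18.1 points, z = 2.41, p = 0.016.
- Missing counted against surgery (0 of 8 recovered v 8 of 8): 60/83 − 53/83 = 7/83 = 8.4 points, z = 1.17, p = 0.24.
- Missing counted for surgery (8 of 8 v 0 of 8): 68/83 − 45/83 = 23/83 = 27.7 points, z = 3.83, p = 0.0001.

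The last two are limits, not forecasts. They show that the planned amount of dropout is enough, at the extreme, to reverse a significant result.

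**4. Whether the mixed model closes the gap.** Section {20b} describes it as accounting for possible confounders. It does not say that the 3-week, 3-month and 6-month values enter as repeated outcomes. Without them, the model also uses only participants with a 12-month value.

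**5. What excluding unmeasurable fingers would do, if it happened.** All rates here are assumed, and unmeasurable fingers are taken as true failures. With 75 per arm and true recovery of 85% v 65%, counting them as not recovered gives 20.0 points and power of 81%. Excluding them divides each rate by the measurable share:

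- 5% surgery v 15% cast unmeasurable: 0.85/0.95 = 89.5% and 0.65/0.85 = 76.5%. The difference is 13.0 points and power 53%.
- 5% v 5%: 0.85/0.95 = 89.5% and 0.65/0.95 = 68.4%. The difference is 21.1 points and power 88%.
- True rates of 70% v 50%, with 5% v 15% unmeasurable: 0.70/0.95 = 73.7% and 0.50/0.85 = 58.8%. The difference is 14.9 points, and power falls from 71% to 45%.

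The direction and size depend wholly on the imbalance between arms.

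**The case against.** The strongest reply is that analysis by allocated arm is kept, that many trials use the intention-to-treat label for observed cases, and that a protocol article leaves missing-data detail to an analysis plan. The first part stands: a reader might infer that intention to treat has been abandoned, and that is too strong, since only completeness fails. The deferral argument does not stand. The no-imputation rule is stated outright, section {31c} presents the article as the complete protocol, and section {20b} excludes further additional analyses.

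A reader might also infer that the plan drops the worst fingers. The documents do not say so. The seven-of-ten sentence follows the description of the test and reads naturally as the pass criterion at each distance. The worst class is open-ended, and a finger that fails at the 10 mm threshold is a known non-recovery needing no imputation. What stands is narrower: no code is stated, so exclusion is permitted but not prescribed.

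A third tempting inference is that "repeated measures ANOVA" would delete every participant who misses a visit across the secondary outcomes. Section {20a} offers it only as an alternative to the t-test, for variables assumed normal (age, range of motion and grip strength). That claim is not made here.

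Finally, the magnitudes rest on assumed inputs, and the documents contain no evidence that losses will differ by arm. This is correct. It limits what can be said about likely bias but does not remove the mismatch between label and analysis.

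**Conclusion.** The point holds in this form: as written, the primary analysis is observed cases by allocated arm, about 16 of 166 randomised participants are expected to be absent from it, and no planned analysis tests how much that matters. Under the assumed counts, a 20-point difference could lie anywhere from 8.4 to 27.7 points. That range assumes 8 missing per arm and the two extreme allocations; it says nothing about which direction is likely.

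The missing code for absent discrimination is a smaller, separate gap in the endpoint definition. It would matter only if such fingers were excluded and were unequally common between arms.

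The change should be made. It concerns a stated rule for the primary result of an open-label trial, and inclusion is expected to run to the end of 2030, so it can be prespecified before the final analysis.

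**What to change.** 1. In the S2PD section, state that a finger tested at 12 months without valid discrimination at the threshold counts as not recovered and stays in the denominator. Give absence of discrimination up to 25 mm an explicit code at every visit, so that earlier results can also be used. The threshold itself must be reconciled: section {14} includes exactly 10 mm as recovery and section {20a} does not.
2. In section {20c}, replace the no-imputation rule with an analysis of all randomised participants by multiple imputation, using the 3-week, 3-month and 6-month S2PD and baseline variables. Report the observed-case result beside it and add a tipping-point check.
3. At minimum, if observed cases remain primary, describe the set as observed cases by allocated arm and prespecify the imputation and tipping-point analyses as sensitivity analyses.
4. In section {20b}, say whether the mixed model uses the repeated visits.

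The cost is revised wording and a little more analysis work, with no new data. Multiple imputation relies on a missing-at-random assumption, which the tipping-point check probes.

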**Methods:**

In this randomized controlled trial, we will allocate patients with injury to a single digital nerve to either surgical nerve repair and cast, or immobilization only. The primary outcome is the return of sensation, measured as static two-point discrimination, at 12 months after injury. Secondary outcomes include complications, the Semmes–Weinstein monofilament test, the Mini Sollerman hand function test, and patient-reported outcome measures.

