### Complications

#### Neuropathic pain/neuroma

Suturing a digital nerve is considered to reduce the risk of neuroma development. Patients with a DN4 score of ≥4 are considered to exhibit signs of neuropathic pain and will undergo further examination.

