### Interim analyses {21b}

An interim analysis of adverse side effects will be conducted during the study. Once 42 patients, representing half of the planned study population, in each group, have completed the 6-month follow-up, the research team will assess the incidence of neuropathic pain. This assessment will be conducted using the DN4 questionnaire. A potential neuroma is considered present if a patient scores ≥4 on the DN4. If *a* ≥ 400% difference is observed in the proportion of patients scoring ≥4 on the DN4 questionnaire between the treatment groups, the study will be terminated due to an unacceptably high incidence of neuropathic side effects. Assessments of function, pain, and unwanted side effects will be conducted during follow-up visits, with regular evaluations of study participants held in collaboration with occupational therapists and researchers. If a patient scores ≥4 on DN4 and does not respond to conservative treatment for neuropathic pain (desensitization), he/she will be assessed by a hand surgeon for further diagnostics.

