### Adverse event reporting and harms {22}

Complications and reported adverse events will be reported. Differences in adverse events between groups will be investigated at the time of the interim analysis and at the completion of the study.

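### Complications are put under an as-treated analysis in {20c}, against the rule in {11b} that all results are by intention to treat, and no comparison by randomised arm is kept

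*Protocol article*

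**What the plan says.** Three statements in the protocol article fix the analysis set.

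- Criteria for discontinuing or modifying allocated interventions {11b}, directly after a sentence on how complications are treated: "All results will be presented according to the intention-to-treat principle".
- Methods in analysis to handle protocol non-adherence {20c}, on the primary outcome: "The main outcome in the final analysis will be presented according to the intention to treat principle".
- The same section {20c}, on harms: "Complications will be handled with an as-treated analysis".

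The abstract gives complications the status of an outcome: "Secondary outcomes include complications". Under Complications, neuropathic pain or neuroma is tied to the DN4 questionnaire: "Patients with a DN4 score of ≥4 are considered to exhibit signs of neuropathic pain and will undergo further examination".

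Interim analyses {21b} bases a stopping rule on a difference "in the proportion of patients scoring ≥4 on the DN4 questionnaire between the treatment groups". It also says that a patient with DN4 of 4 or more who does not respond to conservative treatment is referred on: "he/she will be assessed by a hand surgeon for further diagnostics". Adverse event reporting and harms {22} adds: "Differences in adverse events between groups will be investigated at the time of the interim analysis and at the completion of the study". Neither {21b} nor {22} says whether the groups are those randomised or those treated.

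**The concern.** The two sections give different rules for the same outcome. An analyst who follows {11b} reports complications by randomised arm; one who follows {20c} reports them by treatment received and has no randomised comparison beside it.

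The choice matters because the patients who change group need not be a random sample. In this trial the complication is itself a route to a hand surgeon. If an operation followed and counted as treatment received, the event and the patient would leave the cast group and join the surgery group. The cast rate would fall and the surgery rate would rise, so the error runs in one direction: it makes non-operative treatment look safer. Neuropathic pain is the harm on which the interim rule turns, and the trial is unblinded with no data monitoring committee, so the grouping should be fixed before anyone compares the arms.

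**Working it through.** **1. The rules side by side.**

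| Outcome | {11b} | {20c} |
|---|---|---|
| Primary (S2PD at 12 months) | intention to treat | intention to treat |
| Complications | intention to treat (covered by all results) | as-treated, no other analysis named |

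The sections agree on the first row and conflict on the second. The conflict needs no calculation.

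**2. What as-treated could mean.** The text does not say.

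- Reading A: group by the first treatment actually received. A cast patient operated on later stays in cast, and nothing moves after the start of treatment.
- Reading B: group by any treatment received, including a later operation. A cast patient operated on after a complication is counted under surgery, event included.

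**3. Size under reading B (illustration).** The document gives no complication or crossover rate, so there is no figure of the plan to reproduce for this outcome.

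Input from the document: arm size. Sequence generation {16a} has blocks of 10 + 10 and a last block of 3 + 3 for 166 patients, so each arm has 8 × 10 + 3 = 83.

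Assumed inputs: true risk of DN4 of 4 or more is 20% in cast and 10% in surgery, so 83 × 0.20 = 16.6 and 83 × 0.10 = 8.3 expected events. A fraction f of affected cast patients is later operated on. No one else changes group.

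- Cast as treated: (16.6 − 16.6f) / (83 − 16.6f)
- Surgery as treated: (8.3 + 16.6f) / (83 + 16.6f)

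| f | Cast | Surgery | Difference (points) |
|---|---|---|---|
| 0 | 16.6/83 = 20.0% | 8.3/83 = 10.0% | +10.0 |
| 0.1 | 14.94/81.34 = 18.4% | 9.96/84.66 = 11.8% | +6.6 |
| 0.3 | 11.62/78.02 = 14.9% | 13.28/87.98 = 15.1% | −0.2 |
| 0.5 | 8.30/74.70 = 11.1% | 16.60/91.30 = 18.2% | −7.1 |

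Dividing by 8.3 and setting the two rates equal gives (2 − 2f)(10 + 2f) = (1 + 2f)(10 − 2f), so 20 − 16f = 10 + 18f and f = 10/34 = 0.29. Below that the cast excess shrinks; above it the sign reverses. Under reading A, or by randomised arm, later surgery leaves the first row unchanged.

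With equal assumed counts of 12 in each arm (14.5% each), four such patients give 8/79 = 10.1% for cast and 16/87 = 18.4% for surgery: a difference appears where there is none.

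**4. The interim look (illustration).** {21b} acts at 42 patients per group on a difference of at least 400%. Assume 10/42 in cast and 2/42 in surgery: a ratio of 5, which is a 400% difference. Move one affected cast patient: 9/41 = 22.0% and 3/43 = 7.0%, ratio 3.1, and the threshold is not met. If 400% is read as fourfold, 8/42 against 2/42 meets it, and one move gives 7/41 against 3/43, ratio 2.4. With counts this small, one regrouped patient can decide the outcome of the rule.

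**The case against.** Reporting harms by treatment received is a common convention, and choosing it is not in itself an error. The definition of an as-treated set is often left to a statistical analysis plan, which may exist here.

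The document's timings also favour reading A. Eligibility requires treatment within 10 days of injury, DN4 is first collected at 3 weeks, and referral comes only after conservative treatment has failed. An operation prompted by DN4 would therefore fall outside the treatment window and need not be the allocated nerve repair. The as-treated sentence stands under non-adherence, where the usual meaning is first treatment received against treatment assigned.

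A reader might go further and infer that the plan will move cast patients into the surgery group, often because of the complication. The documents do not support that. {21b} stops at further diagnostics, applies to patients in either arm, and mentions no operation. No section describes crossover from cast to surgery or gives its frequency or reasons. Nor does {21b} say that the interim comparison is as-treated; 42 per group is half of 83 (41.5) rounded up, which fits the randomised arms better, though it does not prove it. A reader might also infer that DN4 will appear by intention to treat in one table and as-treated in another, since it is both a PROM and the complication criterion. The document plans no such tables.

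All of this stands, and it limits the claim about bias to a conditional one. It does not remove the contradiction, and it does not supply the missing analysis by randomised arm.

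**Conclusion.** The point holds as a contradiction with a possible, not a demonstrated, bias. {11b} and {20c} must be reconciled for complications, because {20c} as written leaves the main harm comparison without the protection of randomisation.

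The direction of the possible bias is clear: in favour of cast. Its size is unknown. A cast excess of 10 points would vanish if about 29% of affected cast patients moved, but that rests on assumed risks, an assumed crossover fraction, movement of affected cast patients only, and an as-treated group that counts later surgery. Under first treatment received, later surgery moves no one.

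The change should be made, but it is not critical to the trial's main conclusion: the primary outcome is by intention to treat in both sections.

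**What to change.** In {20c}, state that complications are compared by randomised arm. Keep the as-treated analysis as a supplement, with the group fixed by the first treatment received, and report any later surgery as an event of the randomised arm.

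In {21b}, state that the DN4 comparison uses the randomised arms, so that the interim look and the final report count the same patients in the same groups. In {11b}, add that a supplementary as-treated analysis of complications is the one exception, so that the two sections agree.

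The cost is a few words in each section and one extra table. It needs no new data and does not change the sample size. It should be settled before anyone compares complications between the arms.

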### Plans to give access to the full protocol, participant level-data and statistical code {31c}

This document provides the complete study protocol. Pseudonymized data will be accessible on a reasonable request after the study has been completed.

## Oversight and monitoring

### Composition of the coordinating centre and trial steering committee {5d}

The group responsible for the study reviews the accuracy of the study data on a monthly basis.

